### Secondary safety parameter

7.2

Patients’ routine blood, electrocardiogram, and liver and kidney function tests will be checked at baseline, endpoint, and follow-up of the trial, respectively, aiming to assess the safety of the treatment. All information on adverse events will be recorded at all times, including symptoms of adverse reactions, duration, severity of symptoms, management measures, etiology, and patient prognosis and regression. Investigators record, organize, analyze, and summarize in details.

## Data collection and management

8

The study staff will collect basic subject information, observational indicators, laboratory indicators, and adverse events. Data collators will fill in the above data in the case report form and study medical record. The clinical trial data are traceable and require original information to be stored in clinical charts and databases, with a uniform collective storage method for all case information. All subjects will be replaced by number and no personal information shall be displayed. The clinical trial quality management specifications are strictly enforced throughout the clinical trial process.

### Statistical analysis

8.1

The data statistician of Jiangxi health vocational college of Health Professions will apply SPSS 26.0 (IBM Corp., Armonk, NY, USA) software for data processing. Furthermore, the data statisticians will use descriptive statistics to summarize the baseline situation of the 2 groups. According to the type of data information, we will use the mean and standard deviation to describe continuous variables, dichotomous variables will use the chi-squared test, and rank data will be expressed by non-parametric test. *P* < .05 has statistical significance of differences.

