### Study design

2.1

This is a randomized, double-blind, and placebo-controlled design. A total of 93 patients with painful diabetic neuropathy recruited in this study will be randomized at the ratio of 1:1 to receive treatment and placebo groups for 8 weeks, and the evaluators will assess and analyze the outcomes at 3 time points (pre-treatment, 8 and 10 weeks). The Jiangxi health vocational college will be responsible for data management and statistics. The flow chart of the trial is shown in Fig. 1.

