## Sample size

5

By reviewing the relevant literature,^[23]^ the independent statistician obtained the endpoint mean pain score (MPS). The mean value of the effects of the placebo group was 6.58; the standard deviation of the sample of the placebo group was 1.58; the mean value of the effects of the treatment group was 5.6; the standard deviation of the sample of the treatment group was 1.58. It is logged on the sample size calculation website (https://www.biostats.cn/statx/compute.html), and the relevant parameters were set. The 1-β test efficacy was 0.8 at *α* = 0.05 test level, the ratio of the sample size of the test group to the control group was 1:1, and 42 cases were obtained for the placebo group and the treatment group, respectively. Considering a shedding rate of no >10%, it was designed to include cases, and at least 93 patients should be included in this final clinical trial.

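### The mean pain score comparison that sizes the trial has no stated between-group test, and no use of baseline pain is stated for it; a baseline-adjusted analysis would add power at almost no cost

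*Protocol article*

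**What the plan says.** Section 8.1 (Statistical analysis) works through the data by type: "we will use the mean and standard deviation to describe continuous variables, dichotomous variables will use the chi-squared test". Rank data are given a non-parametric test, and significance is set at P < .05. Baseline appears in that section only as a descriptive summary of the two groups.

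Section 5 (Sample size) takes its inputs from the literature: "the independent statistician obtained the endpoint mean pain score (MPS"). It then gives two means and a common SD: "The mean value of the effects of the placebo group was 6.58", "the mean value of the effects of the treatment group was 5.6" and "the standard deviation of the sample of the placebo group was 1.58", with the same SD in the treatment group. The error rates follow: "The 1-β test efficacy was 0.8 at *α* = 0.05 test level". The result is 42 per arm, taken to 93 in total for dropout of up to 10%.

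Section 2.1 (Study design) has the evaluators "assess and analyze the outcomes at 3 time points (pre-treatment, 8 and 10 weeks"), so pre-treatment values are collected. The Methods part of the abstract lists a pain visual analogue score, SF-36 and nerve conduction velocity among the outcomes.

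**The concern.** Section 8.1 is not simply silent about tests. It goes through the data types, assigns a test to two of them, and gives the third only summary statistics. That third type is the one on which the trial was sized. A reader who follows section 8.1 literally would tabulate the pain scores and stop, without the comparison of means that section 5 powers.

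Two things follow. First, the analyst has an open choice for the pain score (an endpoint t-test, an analysis adjusted for baseline, a rank test) and between the week 8 and week 10 readings. If that choice is settled after unblinding, it cannot be shown to be independent of the data. Second, the plan collects pre-treatment values but states no use of them for the pain comparison, so a gain in precision that needs no further data or patients goes unclaimed.

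**Working it through.** **Inputs from section 5 (Sample size).** Means 6.58 (placebo) and 5.6 (treatment); SD 1.58 in each arm; alpha 0.05; power 0.80; 1:1 allocation; 42 per arm; dropout up to 10%; total 93. Sidedness is not stated.

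**Step 1: reproduce the plan's own figure.**
- Difference = 6.58 − 5.6 = 0.98.
- Standardised difference d = 0.98 / 1.58 = 0.620.
- Normal approximation, two-sided: n = 2 × (1.960 + 0.842)² / 0.620² = 40.8, so 41 per arm.
- Two-sample t-test (noncentral t), two-sided: n = 41.79, so 42 per arm. This is the stated figure.
- One-sided (normal approximation): 33 per arm, which does not fit. The plan is therefore consistent with a two-sided unadjusted t-test on endpoint means.
- Dropout: 84 / 0.90 = 93.3, given as 93.

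**Step 2: power of the implied unadjusted test.** With 42 per arm the noncentrality is 0.620 × √(42/2) = 2.842 on 82 degrees of freedom. Power is 0.802, the planned 80%.

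**Step 3: power with baseline adjustment.** With a baseline-endpoint correlation r, ANCOVA reduces the residual SD to SD × √(1 − r²), so d becomes 0.620 / √(1 − r²). The documents do not give r, so a range is assumed.

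| Assumed r | Residual SD | Adjusted d | Power at 42 per arm |
|---|---|---|---|
| 0 | 1.580 | 0.620 | 0.80 |
| 0.2 | 1.548 | 0.633 | 0.82 |
| 0.3 | 1.507 | 0.650 | 0.84 |
| 0.4 | 1.448 | 0.677 | 0.87 |
| 0.5 | 1.368 | 0.716 | 0.90 |
| 0.6 | 1.264 | 0.775 | 0.94 |

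The covariate costs one degree of freedom (81 instead of 82). At r = 0 this moves power from 0.8020 to 0.8019, so there is no material loss even if baseline pain predicts nothing.

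The entry rule of a pain score above 4 (section 2.3.2) narrows the baseline range, which makes the lower rows of assumed r plausible. At r = 0.3 the gain is about 4 percentage points.

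**The case against.** The strongest reply is that this is a condensed journal article, that an analysis plan may exist, and that baseline adjustment is the kind of detail usually left to it. An unadjusted t-test in a randomised trial is unbiased and controls the type I error, and its standard error already reflects chance imbalance at baseline. Preferring ANCOVA is then a matter of efficiency, not the correction of an error. That stands, and it limits the second half of this point to an improvement. It does not remove the first half, because section 8.1 does assign methods by data type and gives the type used for sizing no test. It could also be said that pain scores might be treated as rank data and so receive the non-parametric test. The article does not say so, and section 5 works with means and SDs.

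A reader might infer more than the document supports:
- That power is lost against the plan. It is not: no test has been fixed, and the test implied by section 5 delivers 0.802.
- That a change-score analysis would undercut the planned power. No section proposes one for pain.
- That all baseline values are ignored. Section 8.1 summarises them by group, section 7.1 compares mean nerve conduction at baseline and endpoint, and section 6 grades response partly by the rise in conduction velocity over its pre-treatment value.
- That the categorical efficacy scale is the only result with inference. Section 7.1 states a comparison of nerve conduction, and the chi-squared test would cover any dichotomous variable.
- That week-8 VAS is the primary outcome. The article names no primary efficacy outcome and does not equate the pain score in section 5 with the VAS.

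**Conclusion.** The point holds in a limited form and should be fixed. The comparison of mean pain scores that sizes the trial has no stated between-group test, and no use of baseline pain is stated for it. This does not put the planned 80% power in doubt. The size of the matter is an unclaimed gain, from 0.80 to between 0.82 and 0.94 at 42 per arm, for an assumed r of 0.2 to 0.6. These figures rest on section 5's difference of 0.98 and SD of 1.58, a two-sided alpha of 0.05, a linear baseline-endpoint relation, and a correlation that the document does not supply. The missing test is established from the text; the amount gained depends on r.

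**What to change.** Add to section 8.1: *The pain score used for the sample size calculation will be compared between groups at the end of treatment (week 8) by ANCOVA, with treatment as factor and the baseline pain score as covariate. The adjusted mean difference will be reported with its 95% confidence interval. Other continuous outcomes will be analysed in the same way, each with its own baseline value, as supportive analyses.* Keep the chi-squared and rank tests for categorical outcomes.

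The same sentence should say which instrument the section 5 pain score refers to, since the article leaves that open. The wording above does not decide which outcome is primary; the sponsor has to state that separately.

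The cost is a few lines of text, to be settled before unblinding. Section 2.1 already provides for pre-treatment assessment, SPSS 26.0 (named in section 8.1) can fit the model, and the sample size stays as planned.

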## Discussion

9

The pathogenesis of PDPN is still unclear, and scholars hold the view that it is multifactorial.^[24]^ Lower limb symptoms are more common than the upper limb, the disease is stabbing pain, burning pain, and drilling pain. Sometimes, severe pain such as amputation pain was aggravated day and night, which could cause foot ulcers, neuroarthritis, and life-threatening.^[25,26]^ Because pain involves central and peripheral mechanisms, there is no specific clinical treatment. Therefore, drugs are mainly used to relieve pain and control the disease.

From the perspective of TCM, the pathogenesis of PDPN is Qi deficiency and blood stasis.^[27]^ The disease is caused by the deficiency of Qi and Yin, obstruction of arteries and veins, and loss of nourishment of tendons. Thus resulting in impeded blood flow of the body, obstruction of arteries and veins, and pain, with clinical numbness of limbs and pain. The principle of treating diseases is to improve Qi and remove blood stasis, relieve pain, and promote blood circulation and collaterals.^[17]^

Mudan granule has the effects of invigorating Qi and relieving pain, promoting blood circulation and removing stasis, and clearing collaterals and relieving pain.^[28,29]^*L chuanxiong* and Rhizoma corylae have the functions of activating blood circulation and removing stasis, Qi and relieving pain. The compatibility of *S miltiorrhiza*, Caulis spatholobi, and Sappanwood can enhance blood circulation and remove stasis. At the same time, with the *P notoginseng* for activating blood and relieving pain and the astragalus for nourishing qi and nourishing blood, it has the effects of removing blood stasis and creating new, and can effectively improve the pain symptoms of patients.

The treatment of PDPN by Mudan granules is not only clinically effective, but also proved to have protective effect on the structure and function of nerve tissue in animal experiments.^[15–17]^ As these conclusions are based on animal experimental studies and controlled studies with low methodological quality, there were no rigorous clinical studies on evaluating the efficacy and safety of Mudan granules in the treatment of PDPN. Therefore, this study intends to explore the efficacy and safety of Mudan granules in the treatment of PDPN through a standard randomized controlled trial.

However, there are still some problems. The sample size of clinical studies is too small to provide sufficient evidence-based medical evidence. It is expected to carry out large-sample, multicenter, and prospective studies in the future. The depth of experimental research on its mechanism of action is not enough, and there still lack researches on the effective components of TCM and the interaction between components in the formula. Therefore, the mechanism of Mudan granule in the treatment of PDPN can be deeply discussed from multiple perspectives and links such as signal pathways.
